### Rewarded training

The reward group will train for 15 h with a version of the METEORS game that is very similar to the one used in previous studies [18, 21]. Briefly, the hand is used to catch the targets that are depicted as meteors. The movement of the patient’s whole arm is displayed with low latency on the computer screen as a moving virtual arm; a feature implemented to increase the feeling for embodiment and thus improve the motivation to move the arm [22]. Subjects are instructed to use the hand to catch the falling meteors in order to protect their planet from being destroyed (Fig. 3a). This game theme is easily understood and emotionally involving [21].

Whenever a meteor is touched by the virtual hand, it explodes, giving the patient immediate knowledge of the result. Furthermore, a score appears with each exploding meteor that depends on the falling speed and diminishes with the time the meteor was visible on the screen before being caught. Scores are summed up over a round and reset when the next round starts. However, there is also an all-time high score always visible on the upper left (Fig. 3a). If a meteor is missed, it crashes on the planet and damages it. Should the patient miss more than four meteors within T_loss < 150 s, the round is lost, which results in visual effects showing the planet being destroyed and the camera shaking, followed by a message encouraging the patient to try again.

After successful level completion, patients are shown a feedback screen illustrating that they have successfully saved the planet, how many meteors they managed to catch and how many they have missed (Fig. 4a). Monetary rewards are given for each completed level. Patients can win up to 1 Swiss Franc (CHF; approx. US$20), if they succeed, but 0.1 CHF is deducted for every missed meteor. As a new level can be started approximately every 3 min, a maximum of 20 CHF could be won per training session in case of an uninterrupted winning streak. This, however, is unlikely due to the difficult adaptation described above. All of it, the money won during the preceding round, during the ongoing training session and the total money gathered over the whole course of the study, is presented on the feedback screen (Fig. 4a), which is followed by a high score list showing the top 10 results (Fig. 4b). If the current result was in the top 10, it is marked in the list (Fig. 4b). This feature was also implemented to optimize patient engagement.

**Fig. 4 Fig4:**
[figure not shown]
ArmeoSenso-Reward feedback screens. **a** “PLANETEN GERETTET”: planet saved. This screen is presented after each completed round. The number of meteors caught (“GEFANGEN”, *top*) and meteors hitting the planet (“EINGESCHLAGEN”, bottom) is indicated on the *left*. The monetary reward (“GEWINN”) for the current round (“DIESE RUNDE”, *top*), the current day (“HEUTE”, *middle*) and the total amount of money gathered over the course of the study (“TOTAL”, *bottom*) are displayed on the right. Note that a maximum of 1 Swiss Franc (CHF) can be won per round. **b** Hall of fame (“RUHMESHALLE”) with the patient’s top 10 scores. If the current score is in the top 10, it is highlighted in *red*

New planets (eight in total) and/or backgrounds (12 in total) are unlocked during the course of the 3-week training. These rewards do not have any influence on the gameplay and difficulty but are intended to add variety to the game. Once three planets have been unlocked, the patient can choose between two randomly selected planets at the start of every round.

### Control training

The control training consists of the same sensor system and game mechanics with all rewarding feedback removed. In order to reduce the feeling of embodiment [22], only the position of the hand is shown as a green decagon on a plain black background. Targets are simple pill-shaped, single-colored objects that disappear with a delay of 1 s without producing a score or sound after being touched; hence, there is no immediate but delayed knowledge of performance. Complete removal of knowledge of performance is not possible in this game because patients then might reach for the same target several times, which would hamper comparability to the other study group. The feedback screen, the monetary reward, the high score list and the unlocking of new planets and backgrounds are also removed. Instead, patients are looking at a blank screen to keep the training time comparable. Most notably, the target placement and difficult adaptation remain unaffected.

### Outcome measures

The clinical assessments are collected by assessors blinded to treatment allocation. All assessors are trained in performing the assessments before the start of the trial. In addition to the outcome measures described below, demographics, comorbidities, cognitive function (Mini Mental State Examination) and concomitant therapy will be recorded (Fig. 5).

**Fig. 5 Fig5:**
[figure not shown]
Standard Protocol Items: Recommendation for Interventional Trials (SPIRIT) Figure. The schedule of enrollment, interventions and assessments

#### Primary outcome

The primary outcome of this trial is the workspace of the impaired arm in the horizontal plane, measured by using an assessment integrated into the ArmeoSenso platform. Subjects are instructed to actively reach out as far as possible with their impaired arm forward, backward and sideways to explore the entire arm workspace. The workspace is corrected for trunk movements and computed as the number of square pixels of 10-cm side length arranged in the transverse plane relative to the patient’s trunk (Fig. 2b) (see Wittmann et al. [18] and Wittmann et al. [21] for more information). This assessment is conducted immediately before and after every therapy session (Fig. 5).

#### Secondary outcome

Arm impairment is assessed using the Fugl-Meyer Assessment-Upper Extremity (FMA-UE), arm activity using the Wolf Motor Function Test (WMFT), the Box and Block Test and a pointing task (ArmeoSenso integrated assessment) (Fig. 5). For the pointing task, nine targets arranged in two semicircles appear one after another in the transversal plane in front of the subject. The goal is to reach out to the target within 8 s. The number of targets reached and the mean time to target is reported. The Motor Activity Log 14 (MAL-14) for self-reported movement ability, the Barthel Index (BI) as a measure of independence in daily living, the National Institutes of Health Stroke Scale (NIHSS) as a measure of stroke severity are recorded and the global disability is assessed using the modified Rankin Scale (mRS) (Fig. 5).

Finally, patients fill in a short questionnaire after each training session. Ten questions (five positively and five negatively formulated), given in randomized order, evaluate the subjective appraisal of the training on a five-point Likert scale (Fig. 5).

#### Assessments of safety

Adverse events (AEs) expected to occur are skeletal or muscular pain and fatigue indicating a syndrome of overuse. The quality management system of the Clinical Trial Center Zurich will be followed according to national and international guidelines [23]. Adverse events (AEs) will be documented and related serious adverse events (SAEs) will be reported to the Ethical Committee, the competent authority (Swissmedic) and local principle investigators (PIs). All SAEs will be included in an annual report to authorities and PIs. AEs will be recorded from baseline assessment to the end of the trial (Fig. 5).

### Sample size

The sample size is estimated to detect a between-group difference of 4.8 voxels in the workspace difference from beginning to end of training, based on the improvement in arm workspace from pilot results (unpublished) and an estimated group difference of 20%. This assumes a two-sided alpha level at .05 and a power of 80%. For an effect with a standard deviation of seven voxels, 35 subjects per group yields 80% power to detect the true alternative. We will randomize 37 subjects in each group, based on our observed attrition rate of 5% in a previous interventional trial [21]. This calculation was performed using G*Power 3.1 [24, 25].

### Statistical analysis

Our primary analysis is an intention-to-treat analysis comparing the two groups. In addition, as this is an explanatory trial, a per-protocol analysis will be used to analyze the effect of feedback under ideal conditions [26, 27]. Therapy will take place in 15 sessions over 3 weeks, and there is the possibility that some subjects will not complete the full treatment regimen due to scheduling issues or other time constraints. If they still perform at least 12 h of therapy the data will be analyzed. All other patients will be considered “non-compliant” in the sense that they do not receive the full treatment dose. According to the per-protocol principle, their outcomes will not be analyzed.

A two-sample *t* test comparing the mean change in voxel workspace assessment between the two groups will be used; in case of non-normality, a Mann-Whitney test will be computed instead. Moreover, repeated measures analysis of variance (ANOVAs), in case of normally distributed data, or non-parametric Friedman tests will be used to assess the development of the different outcome measures over time. Statistical significance will be based on a *p* value threshold of 0.05. Data will be analyzed using MATLAB R2013b (or newer) (MathWorks Inc., Natick, MA, USA) and SPSS (version 23 (or newer), IBM Corp., Armonk, NY, USA).

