### Study population

This study includes stroke patients (maximum 100 days after stroke) who meet the following criteria: minimum age of 18 years, hemiparesis of the arm due to cerebrovascular ischemia, the ability to lift the paretic arm against gravity, a minimal arm workspace of 20 cm × 20 cm in the horizontal plane, ability and willingness to participate, as well as the absence of severe aphasia (i.e., patients who are not able to follow two-stage commands), depression, dementia and hemianopia.

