### Randomization

The randomization procedure was planned and set up by an independent contract research organization (Appletree CI Group, Winterthur, Switzerland). A non-consecutively increasing, pseudo-randomly generated list of subject identification numbers (IDs) was created. IDs are chronologically assigned to each new study participant, stratified by the study center. Allocation to one of the two study groups is balanced in blocks of 4. The randomization list containing the subject ID, the corresponding group allocation and a randomly generated password was sent to an independent (unblinded) study staff member (“admin”) who has set up respective patient-user computer accounts used for accessing the therapy game. The group-specific version of the game, i.e., either with or without reward, is defined by the account. The admin keeps the assignment list and is not involved in data collection.

Immediately before the first training session, each study participant has to confirm by signature to have received a sealed envelope containing a butterfly etiquette with ID and password to access the account. The patient keeps this etiquette for the entire study duration.

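### The primary t test on change is valid, but an ANCOVA on baseline workspace and centre would use the same data more efficiently

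*Protocol article*

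**What the plan says.** All places are in the protocol article.

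- **Statistical analysis:** the named primary method is a *t* "test comparing the mean change in voxel workspace assessment between the two groups will be used". The fallback for skewed data is worded as follows: "in case of non-normality, a Mann-Whitney test will be computed instead". No covariate or stratum is named. The repeated measures ANOVA and Friedman tests in the same paragraph describe how outcomes develop over time and do not adjust the group comparison.
- **Randomization:** "IDs are chronologically assigned to each new study participant, stratified by the study center", in blocks of 4. The section on ethics and reporting gives three clinics.
- **Study population:** "This study includes stroke patients (maximum 100 days after stroke) who meet the following criteria". The criteria include a minimum workspace of 20 cm × 20 cm and set no upper limit on workspace.
- **Primary outcome:** workspace is counted in cells of 10 cm side length, before and after every session, so a baseline value is collected by design.
- **Sample size:** the target is given as "The sample size is estimated to detect a between-group difference of 4.8 voxels in the workspace difference from beginning to end of training". On the spread and the resulting number, the section states: "For an effect with a standard deviation of seven voxels, 35 subjects per group yields 80% power". After allowing for attrition, 37 per group are randomised.

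**The concern.** Two pieces of information that the trial already holds are not used as well as they could be.

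**Baseline workspace.** Analysing the change subtracts baseline with a slope of exactly 1. The entry floor is 4 cells (20 cm × 20 cm on a 10 cm grid) and there is no ceiling, so patients may start with very different workspaces and different room to improve. If the true slope of final on baseline workspace is not 1, the change score keeps variation that an estimated slope would remove.

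**Centre.** Stratified randomisation balances the arms within each clinic, which takes between-centre variation out of the true variance of the group difference. An unstratified *t* test leaves that variation in the estimated standard error. If centres differ, the standard error is too large and the test is conservative.

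The design has almost no power to spare at 35 evaluable patients per arm, so either loss matters more here than in a generously sized trial.

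**Working it through.** **Inputs.** Difference 4.8 voxels, SD 7 voxels (read as the SD of the change), two-sided alpha 0.05, 35 evaluable per group (Sample size section); three centres; blocks of 4. Not in the protocol, and therefore assumed over a range: the correlation r between baseline and final workspace, the ratio k = SD(final)/SD(baseline), and the share of variance due to centre.

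**1. The plan's own figure.** The noncentrality is 4.8 / (7 × √(2/35)) = 2.87 on 68 degrees of freedom. The exact noncentral *t* gives power of 80.7% at 35 per group and 79.6% at 34, so 35 is correct. With 5% attrition, 35/0.95 = 36.8, rounded up to 37. Both stated figures reproduce.

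**2. Adjusting for baseline.** With the change SD held at 7, the residual variance after ANCOVA is 49 × f, where

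f = k²(1 − r²) / (1 + k² − 2rk).

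With equal variances (k = 1) this reduces to f = (1 + r)/2.

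**3. Adding centre.** Baseline plus two centre indicators cost 3 degrees of freedom, leaving 65. To charge for chance covariate imbalance, the residual SD is multiplied by √(1 + 3/65) = 1.023. Centre is assumed to explain nothing, so this is the unfavourable case for including it.

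| r (k = 1) | f | Residual SD | Power, baseline only (67 df) | Power, baseline + centre (65 df, with charge) |
|---|---|---|---|---|
| 0.5 | 0.75 | 6.06 | 90.4% | 89.1% |
| 0.7 | 0.85 | 6.45 | 86.6% | 85.0% |
| 0.8 | 0.90 | 6.64 | 84.6% | 83.0% |
| 0.9 | 0.95 | 6.82 | 82.7% | 80.9% |
| neither covariate prognostic | 1 | 7.00 | 80.7% | 78.9% |

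The comparator throughout is 80.7%.

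**4. Unequal variances.** The slope of final on baseline is r × k, and the gain disappears when that equals 1. For r = 0.8 and k = 1.25, f = 1.5625 × 0.36 / (2.5625 − 2.0) = 1.00: no gain from baseline. For r = 0.8 and k = 1.1, f = 0.4356/0.45 = 0.968 and baseline-only power is 82.0%. For r = 0.9 and k = 1.1, f = 0.2299/0.23 ≈ 1.00: again no gain.

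**5. Ignoring the stratum.** If centre explains a share c of the variance and the arms are balanced within centre, the unadjusted test's true two-sided error is about 2(1 − Φ(1.96/√(1 − c))).

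- c = 5%: 1.96/0.975 = 2.01, error about 4.4%.
- c = 10%: 1.96/0.949 = 2.07, error about 3.9%.

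**6. Simulation** (36 per group, three centres of 24, blocks of 4, 6,000 runs per setting, r = 0.7, k = 1).

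| Centre share | Power, unadjusted | Power, baseline + centre | Type I error, unadjusted | Type I error, baseline + centre |
|---|---|---|---|---|
| 0 | 81.6% | 87.0% | 4.9% | 4.6% |
| 10% | 83.2% | 90.4% | 3.9% | 4.6% |

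**7. Chance baseline imbalance.** With k = 1, the baseline SD is 7/√(2(1 − r)): 7.0 at r = 0.5 and 9.0 at r = 0.7. One standard error of imbalance at 35 per arm is that SD × √(2/35), or 1.7 and 2.2 voxels. Multiplied by (1 − r), it moves the unadjusted difference by about 0.84 and 0.65 voxels, 17% and 14% of the 4.8-voxel target. This is a shift given the imbalance that happened to occur; it averages to zero over randomisations.

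**The case against.** The strongest reply is that nothing in the plan is wrong. A *t* test on change is valid under randomisation, targets the same quantity that the sample size was built on, and delivers the stated power. That stands.

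Four further points also stand, and they limit the claim:

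- A reader might infer that the plan ignores baseline. It does not: a change score subtracts baseline, but with a fixed slope.
- A reader might infer that chance baseline imbalance biases the result. It shifts the estimate only conditionally on the realised imbalance; the estimator is unbiased over randomisations.
- The gain is not guaranteed. It rests on r, k and the centre variance, none of which the protocol gives. The protocol expects improvement in both groups, so the spread may change during training, and a slope near 1 would remove the baseline gain. Nothing in the protocol shows that centres differ.
- Adjustment is not free, nor the only way to protect power from data in hand. It uses degrees of freedom, and the repeated workspace assessments could also be used.

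Ignoring the stratum does not inflate false positives either; the error rate falls slightly below 5%. None of this removes the case for adjustment. The loss is at most about 2 points, the gain is up to about 8 points over r = 0.5 to 0.9 with equal variances and no centre effect, and analysing by the factor used in randomisation brings the standard error into line with the design.

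**Conclusion.** The point holds as one of efficiency. The planned primary test is valid and correctly sized, but it fixes the baseline slope at 1 and leaves out the randomisation stratum. At 35 per arm, adjusting for both takes power from 80.7% to about 81% (r = 0.9), 83% (0.8), 85% (0.7) or 89% (0.5), assuming equal baseline and final variances and no centre effect. It is higher if centres differ, and about 79% if neither covariate is prognostic. If centre explained 5% or 10% of the variance, the unadjusted test would run at about 4.4% or 3.9% in place of 5%. The documents do not support calling the primary analysis biased, invalid or underpowered.

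**What to change.** Make the primary analysis an ANCOVA of end-of-training workspace on group, baseline workspace and centre. Using change as the response gives the same group estimate once baseline is in the model. Report the adjusted difference in voxels with a 95% confidence interval. Keep 37 per group. Keep the unadjusted *t* test, or the Mann-Whitney test where the data are not normal, as a sensitivity analysis. Days since stroke may be added, since the Discussion says that most recovery falls within the enrolment window, but its benefit is not quantified here and it is optional.

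The cost is about 3 degrees of freedom, at most about 2 points of power if neither covariate is prognostic, and a protocol amendment. No new data are needed. With 16 of 74 patients enrolled at submission, the change could be specified before any comparison of outcomes.

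### The primary test switches from a comparison of means to a comparison of ranks if the outcome data look non-normal, so the primary estimand is not fixed

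*Protocol article*

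**What the plan says.** In the protocol article, the Statistical analysis section specifies a two-sample t test: "test comparing the mean change in voxel workspace assessment between the two groups will be used". It then adds that "in case of non-normality, a Mann-Whitney test will be computed instead". The second test replaces the first and is not an addition to it. The significance threshold is 0.05 in either case.

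The Sample size section targets a "between-group difference of 4.8 voxels in the workspace difference from beginning to end of training", with a two-sided alpha of .05, and states: "For an effect with a standard deviation of seven voxels, 35 subjects per group yields 80% power to detect the true alternative". It sets 37 randomized per group to allow for 5% attrition. No calculation is given for a rank-based effect.

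**The concern.** The two tests answer different questions. The t test addresses the difference in mean change, in voxels, which is what the 4.8 refers to. Mann-Whitney addresses whether a patient in one arm tends to have a larger change than a patient in the other. It becomes a statement about a shift in voxels only if the two distributions have the same shape.

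Under the rule as written, the reader cannot know until the outcome data have been examined which of these the primary p value will concern. If the switch occurs, the result does not test the quantity behind the sample size. If the arms also differ in shape or spread, the two tests can disagree: ranks may differ when means do not, or the reverse.

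**Working it through.** **1. The plan's own figure.** Inputs from the Sample size section: difference 4.8, SD 7, two-sided alpha 0.05, power 80%, attrition 5%.
- Standardized effect: 4.8 / 7 = 0.686.
- Noncentral t calculation: n = 34.37, so 35 per group, with power 80.7% at 35.
- Attrition: 35 / 0.95 = 36.8, so 37 per group.

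The stated figures reproduce, and they rest on the t test.

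**2. The same figure under Mann-Whitney, normal data.** Relative efficiency is 3/π = 0.955.
- n = 34.37 / 0.955 = 36.0, so 36 per group.
- With 35 per group the effective size is 35 × 0.955 = 33.4, and power is 78.9%.

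The switch hardly affects the sample size.

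**3. Rejection rates.** Setup: 35 per arm, nominal two-sided 5%, 8,000 simulated trials per row, Monte Carlo standard error √(0.05 × 0.95 / 8,000) = 0.24 percentage points. Assumed trigger, not in the article: Shapiro-Wilk p < 0.05 in either arm.

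| Scenario (means equal) | t test | Mann-Whitney always | Two-stage rule |
|---|---|---|---|
| Same distribution: normal | 5.0% | 4.9% | 5.1% |
| Same: t with 3 df | 4.6% | 5.2% | 5.4% |
| Same: gamma, shape 2 | 5.1% | 5.1% | 5.2% |
| Same: exponential | 4.9% | 5.0% | 5.0% |
| Same: lognormal | 3.7% | 4.5% | 4.5% |
| Gamma v normal, equal SD | 4.9% | 6.9% | 7.0% |
| Exponential v normal, equal SD | 5.2% | 9.1% | 9.1% |
| Gamma, SD ratio 1.5 | 5.1% | 9.6% | 9.6% |
| Exponential v its mirror image, equal SD | 6.3% | 28.5% | 28.6% |
| Exponential, SD ratio 2 | 6.2% | 29.3% | 29.3% |

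With normal data in both arms the assumed trigger still fires in 10.5% of trials.

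**4. Closer to the plan's scale (SD around 7 voxels, equal means).**
- SD 8 v 6: the two-stage rule rejects 6.5% (gamma shape 4) and 8.2% (gamma shape 2).
- SD 10 v 5, gamma shape 2: 16.0–17.1% over repeated runs, against 5.4–5.8% for the t test. In one run, Mann-Whitney used always and the two-stage rule both gave 16.1%.
- SD 10 v 5, normal data: 6.0%, against 5.6% for the t test.

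**5. Reading the results.**
- With one common distribution the rule is close to nominal.
- Unequal spread alone, without skew, does little.
- Where the rate rises, it matches Mann-Whitney used always. The excess arises because Mann-Whitney is not a test of means; the selection step adds almost nothing.
- The t test stays between 3.7% and 6.3% throughout. The low value is conservative and occurs with lognormal data.

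**The case against.** The strongest reply is that the rule is harmless under the null that most readers have in mind. If reward does nothing, both arms share one distribution and the error rate stays at about 5%. This stands. A reader might infer from the switch that the trial's false-positive rate is uncontrolled, but the calculations do not support that. The high rates need a treatment that changes the shape or spread of skewed responses while leaving the mean exactly unchanged. The article gives one SD and nothing on skew, so those scenarios are illustrations.

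A reader might also infer that normality is tested on unblinded data, or that the analyst may report the smaller of the two p values. The article says neither. It names no check, and the word "instead" in the rule excludes a free choice between p values. How non-normality is judged may properly be left to the full protocol or analysis plan, and its absence from the article is not the point here.

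Finally, a rank test has a real advantage in one case: for a pure shift of a strongly skewed distribution (gamma shape 2) its power was about 91% against 81% for the t test. This also stands, and is the price of the fix.

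None of this restores a single primary question. An unseen analysis plan could define the trigger, but as long as the stated switch remains, the data would still choose between means and ranks.

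**Conclusion.** The concern holds as a problem of estimand. The primary analysis may test a difference in means or a difference in ranks depending on the observed outcome, while the trial is sized only for a mean difference of 4.8 voxels. It is worth correcting because it is cheap, but it does not threaten the design: the sample size reproduces, and the error rate is near nominal (4.5–5.4%) when reward has no effect at all.

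Inflation as a test of equal means is conditional: about 6.5–8% at SD 8 v 6 and 16–17% at SD 10 v 5 with skewed data, and up to about 29% in the most extreme case simulated. It belongs to Mann-Whitney as such. All these figures rest on assumed distributions and an assumed Shapiro-Wilk trigger. At about 35 per arm the t test held its level well enough in the same scenarios that the fallback is not needed to protect the error rate.

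**What to change.** State one primary analysis of the between-group difference in mean change in workspace, and run it whatever the distribution looks like. Dropping the switch and keeping the t test is enough to cure the defect. Preferably, adjust for baseline workspace (measured before the first session) and for centre (already a stratification factor), with heteroscedasticity-robust standard errors. That adjustment is an improvement in its own right and not a consequence of the switch. Report Mann-Whitney with the Hodges-Lehmann shift as a labelled sensitivity analysis.

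The cost is wording only. The 35 evaluable and 37 randomized per group are unchanged. The downside is lower power if the true effect is a pure shift of a strongly skewed distribution (about 81% v 91%). The Trial status section reports 16 patients enrolled of the planned 74 at submission, so at that stage the change could be made well before analysis.

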Previous studies have assessed the patient’s motivation for a specific training (e.g., Wittmann et al. [21] and Nijenhuis et al. [29]), but none of them compared the outcome to an appropriate control condition for the evaluation of the effectiveness of rewarding therapy. Although functional improvement itself might be motivating enough for some patients to train, here we are in search of a clinical effect of reward on a reduction in impairment (shoulder/elbow range of motion (ROM)) mediated by active and repetitive proximal-arm training. We chose this training method because (1) it can be standardized in its conduct and has quantifiable parameters of dose, movement success and arm workspace as primary outcome measure, (2) it is based on a therapy system which was already evaluated with patients and found to be safe, (3) it is easily supported in participating institutions without much training of therapists who provide assistance to the patient and (4) it has shown a moderate effect on chronically arm-impaired stroke survivors [21]. Because the ArmeoSenso training only works on proximal-arm function, it is not expected to have a clinically relevant effect on activities of daily living, independence, or quality of life. We therefore chose a primary outcome that is close to what is actually being trained, i.e., arm workspace. Workspace assessments have been widely used to assess the arm function of stroke patients, thereby showing high correlation to standard clinical scales [30, 31]. For a discussion of clinical relevance of functional outcomes, in the interest of clarity and conciseness, we would like to refer to the review by Ashford et al. [32]. Nevertheless, potential transfer to more clinical scores can be tracked using our secondary outcome measures.

The study is enrolling subjects during the initial 3 months after stroke. Most recovery is occurring in this period [33–37]. Therefore, we expect an improvement in arm function in both groups.

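### For non-normal secondary outcomes the only test named is Friedman, which has no group term and so cannot show whether reward changes recovery

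*Protocol article*

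**What the plan says.** The Statistical analysis section of the protocol article has two layers.

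- **Primary outcome.** The section opens with "Our primary analysis is an intention-to-treat analysis comparing the two groups". A two-sample t "test comparing the mean change in voxel workspace assessment between the two groups will be used", and "in case of non-normality, a Mann-Whitney test will be computed instead". This layer compares the groups explicitly and covers workspace only.
- **Outcomes over time.** The next sentence adds that "repeated measures analysis of variance (ANOVAs), in case of normally distributed data, or non-parametric Friedman tests will be used to assess the development". The stated object is "the development of the different outcome measures over time". It names no group factor, no group-by-time term and no other between-group test.

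The Secondary outcome section lists nine instruments: FMA-UE, WMFT, Box and Block Test, pointing task, MAL-14, Barthel Index, NIHSS, modified Rankin Scale and a post-session questionnaire on a five-point Likert scale. The Discussion gives the clinical scores the role of tracking transfer beyond the trained task. On the enrolment window after stroke it says: "Therefore, we expect an improvement in arm function in both groups".

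**The concern.** The plan offers Friedman as the substitute for repeated-measures ANOVA when data are not normal, but the two are not counterparts in a two-arm trial. The ANOVA can include group and group-by-time. Friedman is a one-way, within-subject rank test. Switching from one to the other because of the shape of the data changes the question from whether reward alters recovery to whether patients change at all.

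The primary outcome is a device-based measure chosen to lie close to what is trained. Evidence that any benefit carries over to clinical scales must come from the secondary outcomes, and that is a comparison between arms. For the outcomes that take the Friedman branch, the plan as written gives a p value for recovery and none for reward.

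**Working it through.** **1. The plan's own figure.** Inputs from the Sample size section: difference 4.8 voxels, SD 7, two-sided alpha 0.05, power 80%.
- Standardised difference: 4.8 / 7 = 0.686.
- The normal approximation gives 34 per group. The t-test calculation gives 34.37, rounded up to 35, with power 0.807 at 35 per group.
- Attrition of 5%: 35 / 0.95 = 36.8, rounded up to 37 per group, 74 in total.

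The stated 35 and 37 reproduce. Nothing below affects them.

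**2. What Friedman uses.** For n patients and k visits, with R_j the sum over patients of the within-patient rank at visit j:

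Q = 12 / [n k (k + 1)] × Σ R_j² − 3 n (k + 1)

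Allocation does not appear. Relabelling patients between arms leaves the pooled Q unchanged.

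**3. A worked case.** Assume k = 3 visits (the schedule figure is not shown) and 35 patients per arm, every one of whom improves at each visit.
- Pooled, n = 70: rank sums 70, 140, 210. Σ R_j² = 4,900 + 19,600 + 44,100 = 68,600. Q = (12 / 840) × 68,600 − 840 = 980 − 840 = 140. The 5% critical value on 2 degrees of freedom is −2 ln 0.05 = 5.99.
- Each arm alone, n = 35: rank sums 35, 70, 105. Σ R_j² = 1,225 + 4,900 + 11,025 = 17,150. Q = (12 / 420) × 17,150 − 420 = 490 − 420 = 70 in both arms.

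These values are the same whether the reward arm gains as much as control or several times as much, because only the order of visits within a patient counts.

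**4. Simulation on assumed values.** Settings: 35 per arm, three time points, control gain of 10 voxels, exponential residual with SD 7, 3,000 runs. The voxel scale serves only to give a skewed outcome.

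| True group difference | Pooled Friedman rejects | Mann-Whitney on change rejects |
|---|---|---|
| 0 | 100% | 5.9% |
| 4.8 voxels | 100% | 96.5% |

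The simulation standard error at a true 5% is √(0.05 × 0.95 / 3,000) = 0.4 percentage points, so 5.9% is slightly above nominal. The Friedman column does not move when the group difference does; the Mann-Whitney column does.

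**5. Which outcomes are exposed.** Five of the nine instruments are ordinal or bounded scales where non-normality is plausible: modified Rankin Scale, NIHSS, Barthel Index, MAL-14 and the Likert questionnaire. This is a judgement about such scales; the article gives no distributions.

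**The case against.** **Friedman is not offered as the test of reward.** The sentence is an addition to the primary analysis, and its stated purpose is change over time, which Friedman tests correctly. Rejecting in every run when large gains are built in is proper behaviour for such a test. This is fair, and it limits the point to the absence of any group comparison in that branch. It does not remove the point, because the sentence pairs Friedman with an ANOVA that can carry group, and no other test is named for these outcomes.

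**The article condenses a longer protocol.** Details of secondary analyses may stand there. That would excuse silence. Here, however, a specific test is named, and a fuller document would have to replace or supplement it.

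**Stronger readings the document does not support.**
- A reader might infer that the plan never tests the reward effect when data are non-normal. That is wrong for the primary outcome, where the Mann-Whitney fallback does exactly this.
- A reader might add that the ANOVA will drop many patients with missed sessions, citing "If they still perform at least 12 h of therapy the data will be analyzed". The article does not say that the ANOVA uses all 15 sessions, and it gives no missingness rate. The 12 h floor can also be met with no session missed, since 15 × 48 min = 720 min. Handling of missing data is commonly left to a fuller plan.
- A reader might suppose that separate per-arm Friedman results will be compared to claim a reward effect. The article does not propose this. It is a misuse to rule out, not an error already made.

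**The secondary outcomes are supportive.** The Discussion expects no clinically relevant effect on activities of daily living or independence, which the Barthel Index measures. This lowers the severity.

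**Conclusion.** The point holds for the secondary and longitudinal outcomes. When such an outcome is judged non-normal, the named test has no group or group-by-time term and can show only recovery, which the article already expects in both arms. That follows from the form of the statistic and does not depend on the simulation, which illustrates it under assumed values. How many outcomes are affected depends on their distributions; five of nine instruments are plausible candidates.

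The ANOVA branch could answer the comparative question, but the article does not name group or group-by-time as terms there either.

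The primary comparison, its non-parametric fallback, the alpha level and the sample size all stand. This should be fixed, but it is not critical.

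**What to change.** Amend the sentence on outcomes over time so that:

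1. for each secondary outcome, the inferential test is the between-group comparison of change from baseline to end of training, by t test or, if non-normal, by the Mann-Whitney test the plan already uses for workspace;
2. the repeated-measures ANOVA names group and group-by-time as terms, with group-by-time as the term of interest;
3. Friedman is kept, if at all, as a descriptive within-group analysis, with a statement that per-arm p values will not be compared.

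The questionnaire is filled in after sessions and so has no pre-training value. The plan should say which summary of it the groups are compared on.

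The cost is wording only: no new data, no change in sample size, and no method beyond those already in the plan. The Trial status section reports 16 patients enrolled at submission, so the change could be recorded before any unblinded analysis.
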